### Data collection methods

All patients enrolled into the study will be asked to complete a questionnaire at baseline and again at 6, 12, 18 and 24 months. Given the increasing proportion of patients who have access to the internet it is possible to collect these data online using secure encrypted web-based systems which are a cost-effective alternative to paper questionnaires. At initial enrolment patients will be asked if they have access to the internet and given the option to complete all follow-up questionnaires by mail or electronically. Data entry will be via a web-based system provided by Norwich Clinical Trials Unit Data Management team. Any individual, whether study staff or participant entering data online will gain access to the website using a unique username and password. Participants will only have access to their own data. Once a participant has confirmed the submission of data, they will not be able to change it. The database is built using MS SQL Server and the website and associated software is built using MS ASP.NET. The database and website reside on the Norwich CTU secure server at University of East Anglia. Data from patients who opt to return questionnaires via the post will be entered by a research associate. On receipt of a completed online or paper questionnaire participants will be sent a thank you card and a diary to help them record information about treatments received and out of pocket expenses incurred as a result of the carpal tunnel syndrome for the forthcoming 6 months.

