### Care pathway

The NCS report from the Neurophysiologist will determine the severity of CTS and include treatment recommendations. The clinical management of patients will be at the discretion of the consultant clinical neurophysiologist or referring clinician informed by local guidelines for commissioning and best practice guidelines. Patients who are eligible for the study will fall into three categories: i) no further treatment recommended or required (watch and wait), ii) recommended for conservative treatment by splinting and/or corticosteroid injection; iii) recommended for surgical decompression.

i) No further treatment – patients in this group are expected to have very mild symptoms and NCS confirming a mild compression. They either do not require any conservative treatment or have declined the offer of conservative treatment such as corticosteroid injection.

ii) Conservative treatment – patients in this group are expected to have mild to moderate CTS based on NCS results and will be offered steroid injection and splints.

iii) Surgical treatment – patients in this group are expected to have moderate to severe CTS based on NCS results and self-reported symptom severity. These patients are likely to meet the current thresholds for surgical referral which are: referral to secondary care if symptoms are not resolved to patient’s satisfaction after 6 months of conservative treatment from date of 1st consultation with physician or if neurological deficit is present, i.e. sensory blunting or weakness of thenar abduction (APB).

During the 2 year follow-up, patients may undergo different treatments depending on the course of the CTS. For example a patient may be recommended not to have treatment when first enrolled however 6 months later symptom severity and associated disability may have increased necessitating conservative treatment. Or a patient may be treated with corticosteroid injection initially and progress to surgery in the course of the 2 years. Patients may also seek or be offered other treatments including alternative therapies.

All types of treatments received for CTS of either hand will be recorded by patients through 6 monthly self-report. To assist patients in the recall of treatments received a 6 months diary card will be issued in which they can record date, type, dosage and out of pocket expenditures for any treatments for CTS.

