### Resource use and cost

Patients will be asked to complete a set of resource use questions asking about prescribed medications, primary, secondary and tertiary NHS and private healthcare contacts, alternative therapies and over the counter medicines purchased and time off work due to CTS since the last follow-up. The questionnaire completed at baseline will pertain to resource use in the three months prior to commencement of the study. Following completion of the baseline questionnaire and each follow-up (except final follow-up), patients will be issued with a 'resource use diary’ in the form of a card with tick-boxes and space for notes for patients to complete over the interim time period [23]. This will be used as an aide memoire when completing the resource use sections of the questionnaires.

To verify the patient-self-reported data, at the 2 year follow-up the General Practitioner of a random sample of at least 10% of patients will be contacted to confirm numbers of primary care contacts for CTS, whether the patient is still receiving treatment for CTS, details of drug and dosage where corticosteroid injection has been given, and other drugs prescribed for CTS. Records of surgery performed will also be extracted and compared with patient reported data.

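### The next diary depends on the previous questionnaire coming back and the recall window is not defined after a missed wave, so treatment and cost data in intermittent responders are at risk

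*Protocol article*

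**What the plan says.** Patients are asked to "complete a questionnaire at baseline and again at 6, 12, 18 and 24 months" (Data collection methods). Treatment data come from the same route: "All types of treatments received for CTS of either hand will be recorded by patients through 6 monthly self-report" (Care pathway).

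Two sections tie the next diary to a returned form. Data collection methods: "On receipt of a completed online or paper questionnaire participants will be sent a thank you card and a diary", to be used "for the forthcoming 6 months". Resource use and cost: "Following completion of the baseline questionnaire and each follow-up (except final follow-up), patients will be issued with a 'resource use diary". Care pathway mentions the diary without naming a trigger: "To assist patients in the recall of treatments received a 6 months diary card will be issued".

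The diary is a memory aid and the questionnaire is the data source: "This will be used as an aide memoire when completing the resource use sections of the questionnaires" (Resource use and cost). The same section gives the follow-up recall window as "time off work due to CTS since the last follow-up". By contrast, it fixes the baseline window explicitly, at the three months before the study began.

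**The concern.** The diary is meant to protect self-report against recall error, yet the stated trigger withholds it from patients who have just missed a wave. Their next completed form also carries a window that can be read in two ways, and the answer does not show which reading was used.

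The article's own reasoning makes this relevant. Its Discussion accepts that self-reported resource use is open to recall bias. It supports self-report with evidence on general practice contacts over six months and relies on the diary for accuracy. A missed wave removes the new diary and, on one reading, doubles the recall period.

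Treatment received and two-year cost are at stake. Changes of treatment are the expected course: Sample size expects two thirds of 1070 injected patients to be referred for surgery by two years, that is about 1070 − 355 = 715.

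**Working it through.** **Inputs from the article.** Waves at baseline, 6, 12, 18 and 24 months; a diary after each completed form except the last; 6 months per diary; window since the last follow-up, with scheduled or completed not stated. The article gives no wave non-response rate, so there is no figure of its own to reproduce.

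**Step 1: one patient who misses month 6 and returns month 12.**

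| | Window starts at the scheduled month 6 | Window starts at the last completed form (baseline) |
|---|---|---|
| Months 0–6 | Not asked about | Asked about; the baseline diary is still held |
| Months 6–12 | Asked about, no new diary | Asked about, no new diary |
| Recall length | 6 months | 12 months |
| Effect on the 24-month record | 24 − 6 = 18 months covered (75%) unless the gap is filled | 24 months covered; 24 + 6 = 30 months counted (125%) if months 0–6 are also imputed |

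The percentages are shares of time, not of cost. The error can run either way: 6/24 = 25% of the period missing, or 25% counted twice.

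**Step 2: how many patients could be affected.** Assume each wave is missed independently with probability m. The chance of missing at least one of months 6, 12 and 18 is 1 − (1 − m)³:

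- m = 0.10: 1 − 0.729 = 27%
- m = 0.15: 1 − 0.614 = 39%
- m = 0.25: 1 − 0.422 = 58%

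This count includes patients who miss a wave and never return, so no form of theirs has an ambiguous window. Removing them means subtracting every pattern in which a run of returned forms is followed only by missed ones. With four follow-up waves, the share with a missed wave and a later return is 1 − [(1 − m)⁴ + (1 − m)³m + (1 − m)²m² + (1 − m)m³ + m⁴]:

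- m = 0.10: 1 − (0.6561 + 0.0729 + 0.0081 + 0.0009 + 0.0001) = 1 − 0.7381 = 26%
- m = 0.25: 1 − (0.3164 + 0.1055 + 0.0352 + 0.0117 + 0.0039) = 1 − 0.4727 = 53%

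If all non-response were permanent drop-out, the share would be zero. These figures show possible reach. They do not measure missed treatments or costs.

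**Step 3: the stated safeguards.**

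- *General practitioner check at two years:* a random sample of at least 10% of patients. It covers primary care contacts, injection details and other prescribed drugs. The bias adjustment in Cost of illness analysis applies to primary care cost.
- *Surgery records:* to be extracted and compared with patient report. The text does not make clear whether this covers all patients or the sample, and the Discussion regards primary care records as an imperfect check on secondary care.
- *Missing and censored cost data:* adjustment is planned. It can deal with an absent month-6 form but cannot tell whether the month-12 form already covers that interval.
- *Time off work, out-of-pocket spending and over-the-counter purchases:* no external check is stated.

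**The case against.** The strongest reply is that this is operational detail in a condensed article. Reminders, handling of non-responders and the printed wording of each item normally sit in the full protocol and the questionnaire, neither of which is shown. Care pathway names no trigger for the diary, and nothing forbids sending one after a missed wave. A reader might infer that a diary is sent only after a returned form; the article states a trigger but does not say that it is exclusive. What remains is that two sections state the same rule and one states the window. Carried out as written, these give the result in Step 1.

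A reader might also infer that treatment switches and costs are lost unnoticed and that two-year cost is understated. The documents do not support that:

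- A missed wave is visible, because its form is absent from the database.
- The patient still holds the diary for the interval before the missed wave.
- If the window runs from the last completed form, the missed interval is asked about.
- The Discussion considers patient recall of secondary care fairly reliable, and surgery records are to be compared with patient report.
- Imputing an interval that the next form already covers would overstate cost.

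These replies reduce the problem to a risk of unknown size and direction. They do not remove the ambiguity over whether a form covers 6 or 12 months.

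**Conclusion.** The point holds as a weakness of a stated procedure, confined to self-reported treatment and resource-use data in patients who miss a wave and later return. For them the memory aid is missing for the following 6 months and the next form may cover 6 or 12 months. The possible consequences are under-recall, an unasked interval or double counting; none is certain. The stated safeguards help only in part. The primary outcome, the global assessment at two years, uses neither the diary nor the window.

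The number affected cannot be derived from the article. The 27% to 58% rests on an assumed 10% to 25% non-response per wave and on independence between waves. Under those assumptions it is an upper limit on the share affected, and more permanent drop-out would lower that share. This is a cheap improvement and does not threaten the main analysis.

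**What to change.** 1. Send the diary at months 6, 12 and 18 to every participant who has not withdrawn, whether or not the questionnaire came back.
2. Anchor the resource-use and treatment questions to the date of the last completed questionnaire, pre-filled from the study database on the web and paper forms. If the printed forms already carry such a date, only the diary schedule and the article's description need changing.
3. In the analysis, allocate costs to that dated window and do not impute a missed wave that a later form already covers.

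The cost is one extra diary per non-responder per wave, some postage and a date field on existing forms. The drawback is a longer recall period for those who missed a wave. Recruitment began in July 2013, so forms already returned may carry the undated wording; record which version each form used.

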### Sample size

An estimated 1200 patients are seen at the Norfolk and Norwich University Hospital (NNUH) each year with suspected carpal tunnel syndrome. Of these, at least 85% (around 1020) will be confirmed as having CTS through NCS indicating a mild or worse compression. Assuming a recruitment rate of 75%, which is not unreasonable, given previous experiences, we would expect to recruit around 765 CTS subjects per annum, i.e. 1530 over the two year recruitment period. It is estimated that around 30% (460) will go to surgery immediately and 70% (1070) will be treated with corticosteroid injection. Of the latter, it is expected that, by two years follow-up, two thirds will have been referred for surgery, whereas the remaining third (about 355) will be considered a success. There is no standard agreed method for calculating sample sizes or statistical power for logistic regression models. However, following the approach by Demidenko [24] a sample size of 1070 would confer 90% statistical power, assuming a 33% success rate, to detect an increase in success with an odds ratio of 1.51 for an explanatory binary variable with an even split in classification (i.e. an equal number of subjects in each group). For an uneven split, this odds ratio would be smaller. Should recruitment be less than expected, a sample size of 535 (i.e. half that expected) would confer 90% power to detect an odds ratio of 1.79.

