We were faced with a number of design issues that arose during development of the study, not least in the choice of outcome measures. A review of the literature was undertaken to identify those factors which have been shown to be predictive of outcomes for surgical and conservative treatments. Although a number of studies have explored predictive factors these have been conducted either retrospectively, are based on small sample sizes or have been done in the context of randomised trials which has limitations. Katz et al. [25] studied 241 patients enrolled in a community based study of outcomes for CTS treatment. 78% completed follow-up at 18 months. In a bivariate analysis higher pre-operative symptom severity and functional limitations (measured on Boston Carpal Tunnel Questionnaire [26]), lower mental health status and lower physical health status (measured by SF-12) were associated with worse outcome after surgery. Work-related variables associated with a worse outcome after surgery were being in receipt of workers’ compensation and where an attorney was involved, heavy manual labour and those using repetitive forceful exertions. Linear regression identified greater pre-operative functional limitation, tobacco and alcohol use, worse mental health status, prominent day pain and bilateral symptoms as predictors of worse outcome. Those more intensively exposed to keyboard activities had better symptom status. A study by Meys [11] at al examined prognostic factors for response to corticosteroid injection in a prospective cohort study of 118 patients in the Netherlands. Successful outcome was defined as no need for further treatment within 1 year of injection. 67.4% proceeded to surgery by 1 year. Predictors of successful outcome from steroid injection were a lower Boston symptom severity score, lower median nerve ultrasonic cross-sectional area and lower median nerve swelling ratio.

Other putative factors which have been identified in the literature include duration of symptoms, severity of paraesthesia at night [27], constant paraesthesia and older age [28]. Whilst these studies do not offer any definitive answers they have been useful in identifying putative predictors which should be included in our study.

We therefore chose to measure CTS severity, hand functional status, psychological status, overall health related quality of life, co-morbidities, as well as health service resource use and out of pocket costs.

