Resource use data will be collected by self-reported questionnaire. Such data are at risk of recall bias, [33] although patients in general practice appear to be reasonably accurate in estimating GP contacts over a six month period [34]. Use of a diary as an aide memoire will help ensure fidelity of the data. However, to further verify the patient-self-reported data, we will contact at least 10% of patients’ GPs to confirm primary care activity as described above. Records of surgery performed will also be extracted and compared with patient reported data, although evidence suggests that primary care records are a less than ideal source of validation of secondary care activity [35]. Patient recall for secondary care activity is considered fairly reliable [33].

We chose to include patients with diabetes within the study. Patients with diabetes may or may not also have a diabetic neuropathy. However as this is very difficult to differentially diagnose from the CTS, it would be difficult to apply an exclusion criterion for those with diabetic neuropathy reliably. There will also be a large proportion of patients with diabetes and CTS but no diabetic neuropathy. Thus excluding those with diabetes may significantly limit the number of patients who can be recruited, as well as potentially affecting the generalizability of the results. Moreover by including these patients in the analysis it will be possible to examine the effect of diabetes as a comorbid factor on outcome.

We chose to recruit patients through clinical neurophysiology. This has two advantages: firstly, the diagnosis of CTS will be made through a combination of good clinical examination, history taking and NCS, therefore reducing the risk of treatment failures due to misdiagnosis. Secondly, it provides a single point of recruitment for patients referred from primary and secondary care from a large catchment area in Norfolk/Suffolk. Nevertheless, although it was initially planned as a single centre study, initial recruitment data indicates that the response rate is lower than anticipated and further departments of neurophysiology within the UK will be included subject to local research governance approval.

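### The 90% power is computed on 1070 injected recruits, which leaves no room for the watch-and-wait group or for any loss to follow-up at 24 months

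*Protocol article*

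**What the plan says.** The Sample size section expects 1200 referrals a year, at least 85% confirmed and 75% recruited: "we would expect to recruit around 765 CTS subjects per annum, i.e. 1530 over the two year recruitment period". It divides these recruits in two: "around 30% (460) will go to surgery immediately and 70% (1070) will be treated with corticosteroid injection". Of the injected, "two thirds will have been referred for surgery, whereas the remaining third (about 355) will be considered a success". The power statement follows on the same number: "a sample size of 1070 would confer 90% statistical power, assuming a 33% success rate", for an OR of 1.51 on a binary predictor with an even split. A second figure, 535 patients and an OR of 1.79 at 90% power, is offered in case recruitment falls short.

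Other sections describe a wider cohort and a late outcome:

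- Inclusion criteria admit patients for whom no treatment is currently recommended.
- Care pathway: "Patients who are eligible for the study will fall into three categories". The first is watch and wait, including patients who declined conservative treatment. The second is conservative treatment, which may be splinting, injection or both.
- Outcomes: the primary outcome is a patient-reported global assessment at 2 years.
- Discussion: in a cited carpal tunnel cohort, "78% completed follow-up at 18 months". For this study, "initial recruitment data indicates that the response rate is lower than anticipated", and further centres are to be added.

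**The concern.** Two steps are missing between recruits and analysed patients. First, 30% plus 70% is 100%, so the untreated category that the article enrols has a share of zero in the sample size. Second, 1070 is both the number expected to be injected and the number in the power statement, so every one of them must return a rating 24 months later. The fallback of 535 has the same gap: it is introduced as a recruitment shortfall, and all 535 are again counted as analysed.

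At stake is the sensitivity the article reports for its injection model. A reader takes from it that predictors with an OR of about 1.5 will be found with 90% power. With ordinary loss to follow-up, that is too favourable.

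**Working it through.** **Inputs from the article.** 1200 referrals a year, 85% confirmed, 75% recruited, two years of recruitment; 30%/70% split; success rate 33%; even split of the predictor; OR 1.51 at N = 1070 and OR 1.79 at N = 535; 90% power.

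**Assumptions.** The significance level of the power calculation is not stated; two-sided 5% is assumed because it reproduces the figures, and 33% is taken as the success rate in the reference group. No 24-month response rate is given, so 90%, 78% and 70% are used. The 78% is the cited cohort's figure at 18 months and serves only as a sensitivity value. No share of never-injected recruits is given either.

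**Step 1: recruitment chain.** 1200 × 0.85 = 1020; × 0.75 = 765; × 2 = 1530. Then 0.30 × 1530 = 459 and 0.70 × 1530 = 1071, rounded in the article to 460 and 1070. 460 + 1070 = 1530, so nobody is left for a third category.

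**Step 2: reproduce the stated power.** Wald test of the log OR with one binary predictor:

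power = Φ( ln(OR)/SE − 1.96 ), SE² = [1/(0.5·p0·q0) + 1/(0.5·p1·q1)] / N, where q = 1 − p.

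- OR 1.51: p0 = 0.33, p1 = 1.51 × 0.33 / (0.67 + 1.51 × 0.33) = 0.4265. The bracket is 9.046 + 8.177 = 17.22. With N = 1070, SE = 0.1269; ln(1.51) = 0.4121; ratio 3.248; power = Φ(1.288) = 90.1%.
- OR 1.79, N = 535: power 90.3%.

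Both stated figures are confirmed. If 33% is read as the overall success rate, the results are 88.2% and 87.7%.

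**Step 3: apply 24-month response only.** N = recruits × response; the detectable OR is the one with 90% power at that N.

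| Response (assumed) | N from 1070 | Power for OR 1.51 | Detectable OR | N from 535 | Detectable OR |
|---|---|---|---|---|---|
| 100% | 1070 | 90.1% | 1.51 | 535 | 1.78 (stated as 1.79) |
| 90% | 963 | 86.9% | 1.54 | 482 | 1.84 |
| 78% | 835 | 81.8% | 1.59 | 417 | 1.93 |
| 70% | 749 | 77.6% | 1.63 | 375 | 2.00 |

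For the 78% row: SE = √(17.22/835) = 0.1436; 0.4121/0.1436 = 2.870; Φ(2.870 − 1.960) = 81.8%.

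**Step 4: illustrate the case mix.** If 10% of all recruits were never injected (an assumption with no source in the article), the injected share would be 60%. With 78% response, 1530 × 0.60 × 0.78 = 716, power for OR 1.51 is 75.7%, and the detectable OR is 1.65.

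**The case against.** The strongest reply is that nothing was miscalculated. The statement "a sample size of 1070 would confer 90% statistical power" is a true conditional, and power depends only on the analysed number, however it comes about. By giving 1.51 at 1070 and 1.79 at 535, the article already shows the price of losing up to half the cohort. The main loss scenarios (835, 749 and 716 patients; OR 1.59 to 1.65) lie inside that bracket. This stands, and it limits the consequence. It does not remove the fault: the 535 is offered for low recruitment, the article says response is already below expectation, and loss to follow-up multiplies with that shortfall. The fallback after loss (OR 1.84 to 2.00) lies outside the bracket.

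A second reply is that some watch-and-wait patients will be injected later, as Care pathway allows, and that the same section says the conservative group will be offered both injection and splints. This also stands. The never-injected share is uncertain and could be smaller than the baseline watch-and-wait share. The loss-to-follow-up point does not depend on it.

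A reader might infer more than the article supports:

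- **That the exclusion criteria were forgotten.** The 75% recruitment rate may already absorb ineligible patients, and confirmation is put at 85% as a minimum.
- **That 78% is what this study will achieve.** It comes from another cohort at 18 months.
- **That 716 is the true analysable number.** It rests on an assumed 10%.
- **That the study is invalid or must recruit more.** The effect is a moderately larger detectable OR in a prognostic cohort that the Discussion calls a first step before external validation.

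Adding centres addresses recruitment, but neither case mix nor 24-month response.

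**Conclusion.** The point holds as an inconsistency in the sample-size input. The formula and arithmetic are right; the N of 1070 contradicts the article's own three care categories and assumes complete response at 2 years. This is not a detail left to a fuller document, because the article publishes an exact N, power and OR that its other sections do not support.

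The size is moderate. From loss alone, over an assumed response of 90% to 70%, power for OR 1.51 falls from 90% to between 87% and 78%, and the detectable OR rises to between 1.54 and 1.63. At the fallback it rises from 1.79 to between 1.84 and 2.00. The untreated share makes this worse by an amount that cannot be fixed from the article. All figures assume a two-sided 5% test, a reference success rate of 33% and an even split.

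**What to change.** Restate the sample size on evaluable injected patients: recruits × share injected × 24-month response. Give power and detectable OR as a range over plausible values of the last two factors, for both the main and the fallback recruitment figure, and update them with observed rates as they become available. Reconcile the 30/70 split with the three care categories by giving watch-and-wait and splint-only patients their own expected share, and say how patients injected later are counted. Label any response rate or never-injected share that lacks data as an assumption.

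The cost is a text change in the Sample size section and a less favourable stated OR. No extra recruitment is needed.

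### The 33% success rate is derived as an overall rate, but the stated odds ratios of 1.51 and 1.79 match its use as a reference-group rate; with 33% overall, power is about 88%

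*Protocol article*

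**What the plan says.** All the relevant figures stand in the Sample size section of the protocol article.

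- About 1070 patients are expected to be treated by injection. Two thirds are expected to be referred for surgery within two years, and "the remaining third (about 355) will be considered a success".
- The power statement follows: "a sample size of 1070 would confer 90% statistical power, assuming a 33% success rate". The effect considered is 1.51 on the odds-ratio scale, for a two-category predictor with half of the patients in each category.
- If recruitment falls short, "a sample size of 535 (i.e. half that expected) would confer 90% power to detect an odds ratio of 1.79".

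The power sentence does not say whether 33% is the rate over all patients or the rate in one category of the predictor. It gives no significance level. The only level in the article is the 10% used for univariate screening in the Analysis section.

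**The concern.** For a binary predictor, an overall success rate and a reference-category rate are different inputs. If the odds ratio exceeds 1 and the reference half succeeds at 33%, the other half succeeds more often and the overall rate lies above 33%. The section arrives at a third by counting successes among all injected patients, and a reader will carry that meaning into the power sentence. If the calculation used the figure in the other sense, it assumed more successes than the section expects, and the quoted power is slightly too favourable.

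At stake is the accuracy of two published figures. The fallback figure deserves some care, because the Discussion reports a response rate below expectation, so readers may come to rely on the smaller sample size.

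**Working it through.** **Inputs.** From the Sample size section: n = 1070 and 535, success rate 33%, odds ratios (OR) 1.51 and 1.79, 50:50 split, power 90%. Assumed: two-sided 5% (critical value 1.96) and a Wald test with the variance under the alternative, as the reading of the cited logistic-regression method.

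**Formulas.** With p0 and p1 the success rates in the two halves:

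- p1 = p0·OR / (1 − p0 + p0·OR)
- SE² = 1/[(n/2)·p0(1 − p0)] + 1/[(n/2)·p1(1 − p1)]
- power = Φ(ln OR / SE − 1.96)

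**Step 1: reproduce the plan's figures, with 33% as the reference-group rate.**

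- n = 1070, OR 1.51: p1 = 0.4983/1.1683 = 0.4265. SE² = 1/118.29 + 1/130.86, so SE = 0.1269. ln 1.51 = 0.4121, and 0.4121/0.1269 = 3.248. Power = Φ(1.288) = 90.1%.
- n = 535, OR 1.79: p1 = 0.5907/1.2607 = 0.4685. SE² = 1/59.14 + 1/66.61, so SE = 0.1787. ln 1.79 = 0.5822, and the ratio is 3.259. Power = Φ(1.299) = 90.3%.
- The odds ratios with exactly 90% power are 1.509 and 1.7845, which match the stated 1.51 and 1.79 when rounded up.

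**Step 2: the successes this implies.**

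- n = 1070: 535 × (0.33 + 0.4265) ≈ 405, an overall rate of 37.8%. The section expects about 355, and 355/1070 = 33.2%.
- n = 535: 267.5 × (0.33 + 0.4685) ≈ 214, an overall rate of 39.9%. At 33% overall it would be 0.33 × 535 ≈ 177.

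**Step 3: use 33% as the overall rate.** Solve for p0 so that (p0 + p1)/2 = 0.33.

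- n = 1070, OR 1.51: p0 = 0.285, p1 = 0.375. SE² = 1/108.94 + 1/125.44, so SE = 0.1310, and the ratio is 3.147. Power = Φ(1.187) = 88.2%.
- n = 535, OR 1.79: p0 = 0.266, p1 = 0.394. SE² = 1/52.26 + 1/63.86, so SE = 0.1865, and the ratio is 3.121. Power = Φ(1.161) = 87.7%.
- The odds ratios with 90% power are 1.529 and 1.832. Keeping 1.51 and 1.79 at 90% power would need about 1136 and 578 patients.

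**Step 4: sensitivity of the overall reading.**

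| Variant | n = 1070 | n = 535 |
|---|---|---|
| Two-proportion test, power at the stated OR | 88.5% | 88.2% |
| Two-proportion test, OR with 90% power | 1.526 | 1.822 |
| 1/3 in place of 0.33 (Wald), power at the stated OR | 88.4% | 87.9% |
| 1/3 in place of 0.33 (Wald), OR with 90% power | 1.527 | 1.829 |
| Two-sided 10% (Wald), power at the stated OR | 93.3% | 93.0% |

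At two-sided 10% the reference-group reading gives about 94.6% and 94.7%, so neither reading returns 90% at that level. For the overall reading to return 90%, alpha would have to be about 0.062 at n = 1070 and 0.066 at n = 535; neither is conventional, and they differ. Of the combinations tried, only 33% as the reference-group rate with two-sided 5% gives both stated figures.

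**The case against.** The strongest reply is that the figures do reproduce. The power sentence speaks of an increase in success from an assumed 33%, and an increase can be read as starting from that rate. The 355 is a rounded planning expectation, the predictor is generic, and using an anticipated rate as the reference-group rate is a common simplification. The 405 and 214 are back-calculated here and appear nowhere in the article. This stands in part: the wording admits the reading that reproduces. The text does not state that reading, though, and the only rate it derives is the overall one.

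A second reply is that alpha is not given. That also stands. At two-sided 10%, power under the overall reading exceeds the stated 90%. Two-sided 5% is the likelier level because it reproduces both figures, but it remains an assumption.

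A third is size: about two percentage points of power, in a section that itself warns there is no agreed method and works from round estimates. This stands in full.

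A reader might go further and infer that the stated odds ratios can hold under one reading only, that the 90% is simply false, or that the section contradicts itself. The documents do not support that. The section never says which rate entered the formula, the 90% is right if 33% is the reference-group rate, and the gap otherwise is close to the differences between accepted approximations.

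**Conclusion.** The point holds as a minor imprecision. The section derives 33% over all injected patients, while its odds ratios match a calculation that treats 33% as the rate in the reference half. Under the overall reading, power is lower than stated by 1.8 percentage points at n = 1070 (90 − 88.2) and 2.3 at n = 535 (90 − 87.7). On the sample-size scale the shift is about 6% (1136/1070) and 8% (578/535). Both stated figures err on the favourable side.

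This rests on an even split, a Wald calculation and two-sided 5%, the last of which the article does not state. It does not undermine the study: the sample size follows from expected recruitment, the odds ratios only describe what that number can detect, and no target or analysis changes.

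**What to change.** Choose one of three edits in the Sample size section:

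1. State that 33% is the overall success rate and give the detectable odds ratios as 1.53 (n = 1070) and 1.83 (n = 535).
2. Keep 1.51 and 1.79, state that 33% is the overall rate, and give power as about 88%.
3. If 33% was meant as the reference-group rate, say so and reconcile it with the 355 expected successes, since it implies about 405 of 1070.

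In every case state the alpha and whether the test is two-sided. The cost is one or two sentences and, under the first two options, slightly less favourable figures.
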